## Abstract

**Aims:**

Age-related macular degeneration (AMD) is characterised by a progressive loss of central vision. Intermediate AMD is a risk factor for progression to advanced stages categorised as geographic atrophy (GA) and neovascular AMD. However, rates of progression to advanced stages vary between individuals. Recent advances in imaging and computing technologies have enabled deep phenotyping of intermediate AMD. The aim of this project is to utilise machine learning (ML) and advanced statistical modelling as an innovative approach to discover novel features and accurately quantify markers of pathological retinal ageing that can individualise progression to advanced AMD.

**Methods:**

The PINNACLE study consists of both retrospective and prospective parts. In the retrospective part, more than 400,000 optical coherent tomography (OCT) images collected from four University Teaching Hospitals and the UK Biobank Population Study are being pooled, centrally stored and pre-processed. With this large dataset featuring eyes with AMD at various stages and healthy controls, we aim to identify imaging biomarkers for disease progression for intermediate AMD via supervised and unsupervised ML. The prospective study part will firstly characterise the progression of intermediate AMD in patients followed between one and three years; secondly, it will validate the utility of biomarkers identified in the retrospective cohort as predictors of progression towards late AMD. Patients aged 55–90 years old with intermediate AMD in at least one eye will be recruited across multiple sites in UK, Austria and Switzerland for visual function tests, multimodal retinal imaging and genotyping. Imaging will be repeated every four months to identify early focal signs of deterioration on spectral-domain optical coherence tomography (OCT) by human graders. A focal event triggers more frequent follow-up with visual function and imaging tests. The primary outcome is the sensitivity and specificity of the OCT imaging biomarkers. Secondary outcomes include sensitivity and specificity of novel multimodal imaging characteristics at predicting disease progression, ROC curves, time from development of imaging change to development of these endpoints, structure-function correlations, structure-genotype correlation and predictive risk models.

**Conclusions:**

This is one of the first studies in intermediate AMD to combine both ML, retrospective and prospective AMD patient data with the goal of identifying biomarkers of progression and to report the natural history of progression of intermediate AMD with multimodal retinal imaging.

## Introduction

AMD is the commonest cause of blindness in the elderly. By 2020, 200 million people are expected to be affected with AMD, increasing to nearly 300 million by 2040 [1]. It is a complex, heritable and heterogeneous disease that affects the macula, the central retina that is responsible for detailed central vision. The pathogenesis of AMD is unclear despite intensive research. Drusen are an early clinical feature of the disease and are visualised as yellow deposits predominantly located throughout the macula. However, drusen are also a feature of normal aging adding to the complexity of disease classification. Currently, the severity of AMD is classified into three stages. Early and intermediate AMD are classified based on the size and morphology of drusen and pigmentary changes at the macula while late AMD is characterised by geographic atrophy (GA) and abnormal blood vessel growth. These classification systems do not adequately capture the wide range of phenotypic variation seen in AMD eg the wide range of ‘intermediate AMD’; the lumping together of geographic atrophy (GA) and macular neovascularization (MNV) in ‘advanced AMD’; the absence of acquired vitelliform lesion as a form of AMD etc.

In addition, the inter-individual progression rates of intermediate AMD to advanced forms are extremely variable. For example, currently there are no specific anatomical markers for disease progression that can reliably predict individual risk of conversion to late AMD [2, 3]. Furthermore, AMD classifications are still based on colour fundus photographs despite significant advancement in multimodal imaging of the retina. For example, quantification of drusen volume on OCT is a more reliable quantitative marker than a large drusen identified on colour fundus photographs [4]. However, drusen load is dynamic over time [4]. Therefore, although change in numbers, areas and volume of drusen may provide us with a composite score on overall disease progression, ML may be a better option to identify the fate of each drusen in an eye to understand focal conversion to late AMD. Late AMD may present as geographic atrophy (GA) with atrophy of photoreceptors and retinal pigment epithelium (RPE) in the macula or choroidal neovascularization (CNV) where choroidal blood vessels migrate into the retina and it remains unknown why, when and which markers/events may precede or predict each form of late AMD. If it was possible to predict progression to late AMD this may have ethical implications if no treatments were available to treat it e.g. there are currently no available treatments for GA. Patients would have to be counselled appropriately in this scenario. However, the ability to predict who might progress faster could be advantageous for stratification of patients into clinical trials and in the longer term to allow better personalised medicine if novel treatments are developed as we hope.

Recent advances in imaging technologies have enabled identification of a wide spectrum of potential imaging biomarkers of AMD such as reticular pseudodrusen (subretinal deposits) that develop and progress independently of drusen [5]. Optical coherence tomography (OCT) also indicates that there are 38 different types of drusen that may co-exist in a patient and their significance in AMD progression is unknown [6]. Degeneration of neurosensory layers of the retina was recently shown to play a major role in the prediction of progression to late AMD [7].

Successes in ML during recent years have enabled new applications in medicine and healthcare. In medical imaging, machine learning has been successfully employed for image analysis and interpretation, including [8, 9] the discovery of biomarkers for disease progression and providing decision support for clinicians regarding diagnostic and therapeutic management [10, 11]. In order to exploit these advances to gain better understanding of AMD and provide a personalised risk prediction model for AMD, there are several technical challenges that need to be addressed.

A key challenge is the detection and quantification of changes to retinal structures, which are known to be associated with AMD. This task can be addressed using deep learning techniques which allow highly accurate automated segmentation of anatomical structures. Subsequently, biomarkers such as the volume, density or shape of the segmented structures can be derived and analysed. Using convolutional neural networks, our group has pioneered automated segmentation of intra-/subretinal fluid, hyperreflective foci, neurosensory layers, posterior hyaloid interfaces and the retinal vasculature in AMD eyes [12]. These supervised machine learning approaches have been highly successful as long as there is sufficient training data that has been annotated by human expert observers. Additionally, a hypothesis is needed which structures and associated biomarkers may be of interest.

Another promising avenue is unsupervised biomarker discovery, which can be used to obtain an unbiased, clinically meaningful summary of OCT data. The detected image features can be either directly used for diagnostic or prognostic tasks or presented to clinical experts so that they can formulate hypotheses for new biomarkers. We have recently pioneered this field by defining clinically and genetically distinct disease endophenotypes in nvAMD [13] as well as by discovering so far unknown anomalies in OCT data using a novel technology called generative adversarial networks [14].

The large, natural variability of structure and function across different subjects and populations makes it difficult to determine or learn biomarkers predictive of disease progression. One way of dealing with this heterogeneity is the use of computational models to provide a common reference space. Such spatio-temporal atlases do not only account for anatomic variations and idiosyncrasies of each individual subject, but also offer a powerful framework which facilitates comparison of anatomy over time, between subjects, between groups of subjects and across sites. They have been widely used to capture spatio-temporal processes in the brain, such as neurodevelopment and the progression of Alzheimer’s disease [15–18]. Therefore, a spatio-temporal atlas seeks to define normal anatomy at different ages. It can then be used to extract rules from a machine learning perspective to detect abnormal structural patterns that develop overtime which may be related to abnormal outcomes. In the context of ophthalmology, it could be used to detect structural biomarkers predicting progression to late AMD from OCT retinal images that have been used to create such an atlas of normal retinal ageing.

Finally, decision support tools should support clinical diagnosis and prognosis predictions by making the process more efficient, reliable and objective. Making personalised diagnostic predictions from imaging data is a challenge that can be addressed by combining disease progression models and spatio-temporal models in a statistical model that is learnt from data. There have been initial attempts to do so using machine learning and colour fundus photographs in ophthalmology [15, 19]. There is considerably more information available by utilising optical coherent tomograms (OCTs) of the retina. We have previously used spatio-temporal input features derived from OCT and demonstrated that this approach confers substantial advantages in predicting the future course of retinal disease in terms of prediction of drusen fate on a spatially resolved individual drusen level, progression of AMD on a per-eye level, as well as visual outcomes and treatment intervals in therapy of AMD [17, 20, 21].

## Objectives

Following on from the preliminary work described above the objectives of the PINNACLE study are:To characterise focal and global changes of pathological ageing of the retina to accurately distinguish between health and early pathological changes of AMD disease.To identify and quantify pathognomonic markers and sequence of events preceding cell death and progression to late AMD.To improve accuracy of classification of AMD by building traditional and machine learning models, integrating data from multiple large sources.To create a personalised risk prediction model for progression to late AMD which is accurate and clinically relevant.

## Subjects and methods

### Study design

PINNACLE is a multicentre, non-interventional prospective predictive modelling study with a large-scale retrospective data study running alongside as described below.

### Retrospective study

For the retrospective part of the project, we collected OCT scans of patients 50 years of age or above from routine clinical practice from four university hospital sites: University Hospital Southampton, Moorfields Eye Hospital, Medical University of Vienna, and University Hospital Basel. To increase the rate of healthy subjects, we also integrated OCT data of the UK Biobank biomedical database. In total, this pooled dataset contains more than 400,000 OCT images from almost 100,000 subjects (Table 1).

**Table 1 Tab1:** Sources of OCT scans of AMD patients and healthy subjects that are being pooled in the scope of the retrospective study.

Dataset source	# OCT	# subjects	Comments
University Hospital Southampton	57,875	4251	Primarily acquired with Topcon OCT
Moorfields Eye Hospital	154,371	3956	Acquired with Topcon OCT
Medical University of Vienna	40,626	1649	Acquired with Cirrus OCT
University Hospital Basel	15,976	618	Acquired with Spectralis OCT
UK Biobank	175,869	85,721	Mostly healthy eyes (Topcon OCT)
Total	444,717	96,195	

These images are centrally pseudonymised, standardised, preprocessed and stored. With the help of the associated clinical records, the data is filtered and curated into OCT scans of healthy eyes (negative control), and scans of AMD patients, which will be further stratified into eyes with early AMD (at risk population) and eyes with late AMD (positive control). For many patients, OCT scans taken at multiple timepoints are available that display the longitudinal progression of the disease and healthy aging. A subset of the longitudinal dataset will be labelled by retinal experts. For this purpose, fellow eyes of eyes under treatment with frequent follow-up will be manually graded for conversion from normal retina to AMD based on the presence of soft drusen. These treated eyes may have had treatment for a variety of reasons eg late AMD or retinal vein occlusion. For conversion to advanced neovascular AMD grading will be based on the presence of intraretinal or subretinal fluid, pigment epithelial detachment and subretinal hyperreflective material. Grading of conversion to advanced atrophic AMD will be based on the presence of complete retinal pigment epithelium and outer retinal atrophy (cRORA) [22]. Additionally, experts may identify and label relevant retinal structures in a subset of images.

Using this large retrospective dataset of AMD patients and healthy subjects, we aim to automatically quantify and track the development of known indicators (OCT biomarkers) of retinal aging and AMD. We will train and employ image segmentation algorithms to localise and segment anatomical structures, such as neurosensory retinal layers, vasculature, drusen, hyperreflective foci, intra-/subretinal fluid, pigment epithelial detachment, subretinal hyperreflective material and early signs of geographic atrophy [23].

We can only curate a limited amount of training data for these algorithms due to the costly and time-consuming nature of manual data annotation by clinical experts. In order to still benefit from the large number of OCT images, we will explore the use of self-supervised pretraining. Self-supervised pretraining teaches neural networks to extract semantic information without the need for labelled training data [23, 24]. It may facilitate the use of deep learning with small labelled training datasets or boost its peak performance compared to conventional one-stage training.

Beyond the use of machine learning to extract known retinal features, we aim to use unsupervised machine learning to identify and define novel imaging biomarkers that predict disease progression, characterise AMD and classify subjects into different populations (i.e. fast progressors versus slow progressors). We will construct a spatio-temporal atlas that enables us to compare the retinal anatomy across time for an individual subject, between subjects and between different groups of subjects [25, 26]. It is expected that such atlas and associated representations will facilitate identification of structural changes in the outer retina over time that may shed light on the biological process by which these changes convert to late AMD.

Informed by these findings, we will design and train AI-based prognostic models capable of: (i) predicting the onset of early/intermediate AMD from scans of healthy retina, and (ii) predicting the onset of late neovascular and/or late atrophic AMD from scans of retina with intermediate AMD. The first model would provide a risk estimate (time to event) of AMD onset, providing an insight into AMD risk factors, while the second model will provide a risk estimate (time to event) of advanced AMD onset, providing an insight into risk factors for AMD progression, which will be crucial for patient management and to start a timely treatment for both neovascular and atrophic AMD stages.

The utility of all biomarkers and derived prognostic models will be validated using a separate partition of the large retrospective dataset and generated labels. The multicentre data and different OCT scanners used allow us to assess their generalisability. Ultimately, the identified biomarkers and models will be benchmarked in the prospective study, where an exploratory outcome will be how accurately they predict progression to focal event development.

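### Validating health-versus-early-AMD markers on a partition of the pooled retrospective data can reward recognition of the data source, because most healthy subjects come from UK Biobank and AMD scans mainly from four hospitals

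*Protocol article*

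**What the plan says.** The first objective of the protocol article is to characterise retinal changes "to accurately distinguish between health and early pathological changes of AMD disease". The Retrospective study section describes the data. From the hospitals, "we collected OCT scans of patients 50 years of age or above from routine clinical practice from four university hospital sites". Then: "To increase the rate of healthy subjects, we also integrated OCT data of the UK Biobank biomedical database". Table 1 annotates the UK Biobank row "Mostly healthy eyes (Topcon OCT". Of the hospitals, Moorfields is listed as Topcon and Southampton as mainly Topcon. Vienna is marked "Acquired with Cirrus OCT" and Basel "Acquired with Spectralis OCT".

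After pooling, "the data is filtered and curated into OCT scans of healthy eyes (negative control), and scans of AMD patients", and the AMD scans are divided further into early and late disease. Fellow eyes of treated, frequently followed eyes are to be graded by hand for conversion from normal to AMD. The section also plans a spatio-temporal atlas, which the Introduction describes as defining normal anatomy by age so that abnormal patterns can be detected.

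On validation, the section says that the biomarkers and prognostic models "will be validated using a separate partition of the large retrospective dataset and generated labels". The next sentence says that the range of centres and scanners makes it possible to assess generalisability. The models are then to be benchmarked prospectively on progression to a focal event.

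**The concern.** One database was added to supply healthy subjects, while the other four sources are hospital patients. In such a pool the label (healthy or AMD) and the source are strongly associated. A network can then separate the classes partly through acquisition protocol, image quality or population differences that have nothing to do with retinal disease.

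If the held-out part has the same mix of sources, it has the same association. It then rewards the shortcut and cannot reveal it. The prospective study offers no second check on this contrast, because it enrols only patients with intermediate AMD and its outcome is progression. At stake is the accuracy reported for objective 1 and for any abnormality score read against the atlas.

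**Working it through.** **Inputs (Table 1).**
- Hospital scans: 57,875 + 154,371 + 40,626 + 15,976 = 268,848. Adding 175,869 from UK Biobank gives 444,717, as stated.
- Hospital subjects: 4,251 + 3,956 + 1,649 + 618 = 10,474. Adding 85,721 gives 96,195, as stated.

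**Share of UK Biobank.** Subjects: 85,721 / 96,195 = 89.1%. Scans: 175,869 / 444,717 = 39.5%. Scans per subject: 2.05 in UK Biobank, against 268,848 / 10,474 = 25.7 in the hospitals.

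**Is UK Biobank the main source of healthy eyes?** By subject, yes. If only 51% of its subjects are healthy, that is about 43,700, roughly four times all 10,474 hospital subjects. By scan, it is the main source unless the healthy fraction in the hospitals exceeds 0.90 × 175,869 / 268,848 = 59% (UK Biobank 90% healthy), or 33% (UK Biobank 51% healthy).

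**What a source-only rule would score.** The rule calls every hospital scan AMD and every UK Biobank scan healthy. Let x be the healthy fraction in UK Biobank and y that in the hospitals. Neither is in the document, so both are assumptions. With U = 175,869 and H = 268,848:

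- specificity = xU / (xU + yH)
- sensitivity = (1 − y)H / ((1 − x)U + (1 − y)H)
- AUC = (sensitivity + specificity) / 2

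For x = 0.90 and y = 0.30, specificity = 158,282 / 238,937 = 0.662, sensitivity = 188,194 / 205,781 = 0.915, and AUC = 0.788. The last column repeats the calculation with subject counts.

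| x | y | Specificity (scans) | Sensitivity (scans) | AUC (scans) | AUC (subjects) |
|---|---|---|---|---|---|
| 1.00 | 0.10 | 0.867 | 1.000 | 0.934 | 0.994 |
| 0.95 | 0.20 | 0.757 | 0.961 | 0.859 | 0.818 |
| 0.90 | 0.30 | 0.662 | 0.915 | 0.788 | 0.711 |
| 0.99 | 0.00 | 1.000 | 0.994 | 0.997 | 0.962 |
| 0.60 | 0.50 | 0.440 | 0.656 | 0.548 | 0.520 |

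The last two rows are the extremes of a wider grid (x from 0.60 to 0.99, y from 0 to 0.50): AUC 0.55 to 0.997 by scan and 0.52 to 0.96 by subject. The first row, with x = 1.00, lies outside that grid.

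**How much of this is scanner make?** Little. Southampton and Moorfields supply 57,875 + 154,371 = 212,246 of 268,848 hospital scans (79%), mainly on the same make as UK Biobank. The Cirrus and Spectralis scans are 40,626 + 15,976 = 56,602 (21%). A rule that calls only those AMD, treating all Southampton scans as Topcon, has a scan-level AUC of 0.56 to 0.59 for x of 0.90 or 0.95 and y of 0.10 or 0.30.

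**Within one source.** The source is then constant, so a source-only rule has AUC 0.50 by construction.

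**Limit of the calculation.** Every non-healthy scan counts as a case, including late AMD. The early and late shares by source are not given, so the figure for healthy versus early AMD could differ. It would be lower if late disease is concentrated in the hospitals.

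**The case against.** The strongest reply has four parts.

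1. *The partition is not the only check.* A reader might infer that it is. The text does not support that, because the next sentence announces an assessment of generalisability across centres and scanners. This stands. But comparing centres or scanners does not by itself separate label from source while one database supplies most healthy subjects.

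2. *The type of split is not stated.* A condensed article may leave it to a fuller plan, and a split by site would behave differently from a random one. This is fair as far as it goes. Yet holding out a hospital does not provide a comparison of healthy and early-AMD eyes from the same source unless both are scored there, and the article does not commit to that.

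3. *No pooled classifier is promised.* Both prognostic models start from eyes in a single state. Conversion labels come from frequently followed fellow eyes, which points to hospital data, and known biomarkers rest on expert-annotated segmentation. This limits the scope. It leaves objective 1, the unsupervised markers used for that contrast, and the atlas.

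4. *Disease status is not the same variable as scanner.* A reader might infer this from the Cirrus and Spectralis entries. The figures do not support it, since 79% of hospital scans come from mainly Topcon sites. Nor is the association complete: UK Biobank is only mostly healthy, and the hospitals hold some normal fellow eyes. The stated standardisation and preprocessing may help, but the article describes no step that removes source differences.

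**Conclusion.** The concern holds for markers meant to distinguish health from early AMD, including atlas-based detection of abnormality. Pooled validation can reward recognition of the source through acquisition protocol, image quality and population, and only in small part through scanner make. The prospective cohort has no healthy eyes with which to test this.

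The inflation is possible, not demonstrated, and its size is unknown. The scan-level range of 0.79 to 0.93 rests on assumed healthy fractions, and the wider grid of 0.55 to 0.997 shows how strongly the result depends on them.

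A reader might go further and conclude that the study's main results are compromised or that the problem cannot be put right. The document does not support either. The intermediate-to-late AMD model does not use the health-versus-AMD contrast. The primary analysis is a Cox model in a prospective cohort with intermediate AMD, with OCT on one platform, so neither is directly affected. The remedy is a different analysis of data already being collected. This is a worthwhile, inexpensive improvement to the stated check.

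**What to change.** In the validation paragraph of the Retrospective study section, state that:

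- Health-versus-early-AMD performance will be reported within source: at least within the hospital data, and by hospital and scanner where numbers allow, using the normal and early-AMD fellow eyes already due to be graded.
- It will be reported within UK Biobank only where early-AMD labels exist. The grading described does not clearly provide them.
- Development and validation sets will be split by subject.
- A pooled AUC will not be the headline result for this contrast.

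As diagnostics only, report the AUC of a source-only classifier and an age-matched comparison of the marker between normal hospital eyes and healthy UK Biobank eyes. Neither should be a pass/fail rule. The normal hospital eyes are fellow eyes of treated eyes, some treated for late AMD, and may carry real preclinical change that a valid marker ought to detect.

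The change affects wording and analysis. The within-hospital part needs no new images and uses grading already planned. The cost is fewer healthy eyes per comparison, hence wider intervals and probably a lower reported accuracy. The number of normal fellow eyes is not given, so the loss of precision cannot be sized from the article.
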